# A pilot randomised double blind controlled trial of the efficacy of purified fatty acids for the treatment of women with endometriosis-associated pain (PurFECT): study protocol

**DOI:** 10.1186/s40814-018-0274-8

**Published:** 2018-04-25

**Keywords:** Endometriosis, Purified fatty acids, Chronic pelvic pain, Pilot trial

## Abstract

**Background:**

Endometriosis affects 6–10% of women and is associated with debilitating pelvic pain. It costs the UK > £2.8 billion per year in loss of productivity. Endometriosis can be managed by surgical excision or medically by ovarian suppression. However, ~ 75% symptoms recur after surgery and available medical treatments have undesirable side effects and are contraceptive. Omega-3 purified fatty acids (PUFA) have been shown in animal models to reduce factors that are thought to lead to endometriosis-associated pain, have minimal side effects, and no effects on fertility. This paper presents a protocol for a two-arm, pilot parallel randomised controlled trial (RCT) which aims to inform the planning of a future multicentre trial to evaluate the efficacy of Omega-3 PUFA in the management of endometriosis-associated pain in women.

**Methods:**

The study will recruit women with endometriosis over a 12-month period in the National Health Service (NHS) Lothian, UK, and randomise them to 8 weeks of treatment with Omega-3 PUFA or comparator (olive oil). The primary objective is to assess recruitment and retention rates. The secondary objectives are to determine the effectiveness/acceptability to participants of the proposed methods of recruitment/randomisation/treatments/questionnaires, to inform the sample size calculation and to refine the research methodology for a future large randomised controlled trial. Response to treatment will be monitored by pain scores and questionnaires assessing physical and emotional function compared at baseline and 8 weeks.

**Discussion:**

We recognise that there may be potential difficulties in mounting a large randomised controlled trial for endometriosis to assess Omega-3 PUFA because they are a dietary supplement readily available over the counter and already used by women with endometriosis. We have therefore designed this pilot study to assess practical feasibility and following the ‘Initiative on Methods, Measurement, and Pain Assessment in Clinical Trials’ recommendations for the design of chronic pain trials.

**Trial registration:**

ISRCTN44202346

## Background

Endometriosis is an inflammatory condition that affects 6–10% of women in the UK [1] and is responsible for approximately 20% of gynaecological consultations. It is associated with chronic pelvic pain, pain during menstruation, pain during intercourse, and an increased likelihood of infertility [2]. Endometriosis is associated with a 45% reduction in work productivity with the annual cost for caring for women with endometriosis estimated at > £2.8 billion in the UK [1].

Endometriosis is defined by the presence of endometrial-like tissue (endometriosis ‘lesions’) outside the uterine cavity, most commonly on the pelvic peritoneum or ovaries [2]. The cause of the painful symptoms experienced by women with endometriosis is not well understood. Endometriosis is treated by surgical excision or medical management by ovarian suppression. However, up to 75% symptoms recur after surgery and medical treatments have undesirable side effects [3] and are contraceptive. There is an unmet need for new medical treatments for endometriosis.

An ideal therapy for endometriosis would (i) reduce the painful symptoms associated with the condition, (ii) reduce lesion size, (iii) preserve the patients’ ability to conceive while on medication, and (iv) have no, or limited, side effects. Oral Omega-3 purified fatty acids (PUFA) have the potential to meet all of the above criteria. Omega-3 PUFA are a Food and Drug Administration (FDA)-approved dietary supplement, which play a role in the regulation of prostaglandin metabolism and cytokine physiology, and are thought to work by competing with Omega-6 PUFA to produce lipid mediators which are anti-inflammatory as opposed to pro-inflammatory [4]. Intake of food with a high content of Omega-3 PUFA have been used in other inflammatory conditions, such as atherosclerosis, asthma, and rheumatoid arthritis and have been shown to have an anti-inflammatory effect [5].

In endometriosis, Omega-3 PUFA supplementation has been shown to reduce lesion size and reduce local prostaglandin/cytokine production in a rat model [6]. In an endometriosis model using Fat-1 mice, in which Omega-6 can be converted to Omega-3 PUFA, the number and weight of endometriotic lesions 2 weeks after inoculation were significantly less than in Fat-1 mice compared to controls who cannot convert Omega-6 to Omega-3 PUFA [7]. In vitro studies, using endometrium from women with and without endometriosis have shown that Omega-3 PUFA might have a suppressive effect on endometrial cell survival [8]. In a large, prospective cohort study investigating dietary exposure and endometriosis risk in women, it was concluded that increasing Omega-3 PUFA intake might be the first identified modifiable risk factor for endometriosis [8]. Finally, it is reported that a low ratio of Omega-3 to Omega-6 PUFA intake is correlated with painful menstruation and a high rate of autoimmune and endocrine disorders in women with endometriosis [9].

We believe that it is important to determine the true value of Omega-3 PUFA for the control of or potential elimination of endometriosis-associated pain. A definitive evaluation of the efficacy of Omega-3 PUFA in the management of endometriosis-associated pain will require a large, multicentre randomised controlled trial. This protocol outlines a pilot study to assess the processes that are unknown and vital to the delivery of such a trial, including variance of the response, variables for sample size calculation, follow-up rates, and ‘failure to comply with treatment’ rates. In the pilot study, we are using olive oil capsules, which do not contain Omega-3 PUFA, as a comparator due to lack of availability of a matched placebo. We accept that this comparator might have the potential for pain relief which could encourage participation in our trial and that it might have a unique taste with a theoretical risk of unblinding the trial medication.

## Methods/design

### Study design

We aim to perform a two-arm, parallel, double blind randomised controlled pilot trial (Fig. 1).

**Fig. 1 Fig1:**
[figure not shown]
Flow chart for the trial process

### Study settings

We will recruit patients from gynaecology outpatient clinics, gynaecology wards and day surgery units within NHS Lothian, UK (Royal Infirmary of Edinburgh and St. John’s Hospital).

### Study participants

Women with a surgical diagnosis of endometriosis and associated pelvic pain will be recruited.

### Primary objective

The primary objective is to assess recruitment and retention rates. Recruitment is defined as the proportion of eligible patients who agreed to participate from the number approached. Whereas retention is defined as the proportion of the participating patients who completed both baseline and follow-up visits.

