### Co-primary outcomes

Recruitment and retention rates

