### Participant enrolment

All gynaecology consultants within NHS Lothian will be sent an email informing them of the study and requesting permission to approach their patients. A clinical research fellow will approach eligible women who have agreed to be seen by the trial team, while the women are still in the clinic, provide them with patient information sheets and offer them the opportunity to discuss the trial. Consent will only be taken later once the patient has had ample time, of at least 24 h, to read the patient information sheet. A further appointment will be arranged for the participant to come for this visit.

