### Screening

Eligibility for randomisation will be based on the worst of four weekly numerical rating scale (0–10; NRS) pain scores collected by text messaging (‘run-in phase’), score of 4 out of 10 in 2 or more weeks is required. Texts will be sent by the clinical research fellow to the women’s mobile phone, asking about average and worst pain, respectively, and the woman will be asked to reply to the text message with her pain score, rating it from 0 for no pain at all, to 10 being worst pain imaginable. To capture known cyclicity in pain in women, these texts will be sent once per week during the eligibility phase (weeks–minus one to minus four). If a woman has an NRS of greater than or equal to ≥ 4 in two or more of the pre-randomisation run-in weeks of the study, she will be eligible for randomisation.

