### Sample size

The emphasis in this study is to establish feasibility, not statistical significance. This study is designed primarily to explore the recruitment and retention rates, and we will aim to recruit as many women as possible over a 12-month period. We estimate that we will recruit ~ 4–5 patients per month and will aim to recruit 40 patients. As we anticipate a recruitment rate of 50%, 40 participants would be able to give 95% confidence interval of 35–65%. The data from this pilot study will be used to refine sample size calculations for any future RCT.

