### Data analysis

#### Recruitment and retention rates

Using the information collected from the participant log, we will determine the number of patients recruited from the pool of eligible women and a > 50% recruitment will be deemed acceptable. While a retention rate of 100% would be ideal, we will consider a rate of 80% satisfactory. We will provide an estimate of the proportion and its 95% confidence interval. In addition, we will determine the nature and number of unanswered questions in each questionnaire. We aim to determine whether the trial design will perform well enough in the field to warrant rolling out the study to full trial. All analysis will be carried out at the University of Edinburgh.

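### The co-primary recruitment rate is defined over women approached, but its >50% criterion is applied to the pool of eligible women, and near 50% the two can give opposite verdicts

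*Protocol article*

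**What the plan says.** Recruitment is one of two co-primary outcomes (Co-primary outcomes: "Recruitment and retention rates"). The places that bear on how it is calculated are these.

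- **Primary objective:** "Recruitment is defined as the proportion of eligible patients who agreed to participate from the number approached". The numerator is agreement to participate and the denominator is women approached.
- **Data analysis, Recruitment and retention rates:** "we will determine the number of patients recruited from the pool of eligible women", and in the same sentence "a > 50% recruitment will be deemed acceptable". Here the denominator is the eligible pool, and this is the only place that sets a criterion for recruitment.
- **Participant enrolment:** "A clinical research fellow will approach eligible women who have agreed to be seen by the trial team". Consultants are also first asked for permission to approach their patients.
- **Participant log:** women who meet the eligibility criteria, women invited, women recruited and women who leave early are listed as separate entries.
- **Inclusion criteria and Screening:** a pain score of at least 4 is an inclusion criterion, and "Eligibility for randomisation will be based on the worst of four weekly numerical rating scale (0–10; NRS) pain scores collected by text messaging" during the four-week run-in.
- **Sample size:** the trial "will aim to recruit 40 patients", and "As we anticipate a recruitment rate of 50%, 40 participants would be able to give 95% confidence interval of 35–65" (per cent).

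**The concern.** The criterion sits on a different ratio from the one defined. An eligible woman whose consultant does not give permission, or who declines to be seen by the trial team, belongs to the eligible pool but not to the women approached. The eligible pool is therefore at least as large as the approached group, and the rate over the pool is at most the rate over women approached.

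The word eligible adds a second difficulty. The pain-score criterion is settled only by the run-in, so full eligibility cannot be known when a woman is approached. If eligible in the Data analysis section meant having passed the run-in, that status could not be observed for anyone who never supplied run-in scores.

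At stake is the pilot's main conclusion: whether recruitment was acceptable, and so whether the design works well enough to go on to a full trial. A rate among women approached also says nothing about those lost before approach. If it is read as overall uptake, the multicentre trial would be planned on too high a figure.

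**Working it through.** **1. The plan's own figure.** Inputs from Sample size: rate p = 0.50, n = 40. Formula: p ± 1.96 × √(p(1 − p)/n).

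- 0.50 ± 1.96 × √(0.25/40) = 0.50 ± 0.155, that is 34.5% to 65.5%. The stated 35–65% is reproduced, but only with 40 as the **denominator**.
- The same section makes 40 the number to be recruited, which is the **numerator**. At 50% the denominator is 40/0.50 = 80, and 0.50 ± 1.96 × √(0.25/80) = 0.50 ± 0.110, that is 39.0% to 61.0%.

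So the denominator is not held constant in the Sample size section either.

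**2. How close the anticipated result is to the criterion.** With 40 recruited, a denominator of 79 gives 40/79 = 50.6%, which passes. A denominator of 80 gives 50.0%, which is not above 50%.

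**3. Effect of the denominator.** Assumptions: the women approached are a subset of the eligible pool, a share s of the pool is approached, all recruited women come from those approached, and the criterion is applied to the point estimate. Then

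rate over pool = s × rate over approached,

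and a rate r above 50% among those approached stops passing over the pool once s ≤ 0.50/r. The article gives no counts, so 70 and 75 approached and all values of s are assumed, with 40 recruited. Pools are rounded to whole women.

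| Approached | Rate over approached | s = 95% | s = 90% | s = 80% | s = 70% |
|---|---|---|---|---|---|
| 75 | 53.3% | 40/79 = 50.6% | 40/83 = 48.2% | 40/94 = 42.6% | 40/107 = 37.4% |
| 70 | 57.1% | 40/74 = 54.1% | 40/78 = 51.3% | 40/88 = 45.5% | 40/100 = 40.0% |

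The break-even share is 0.50/0.533 = 93.75% with 75 approached and 0.50/0.571 = 87.5% with 70 approached. In both cases the pool is then 80.

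**4. Eligibility timing.** Setting Participant enrolment beside Screening, a woman is called eligible when she is approached, while eligibility for randomisation is decided later by the run-in scores. Only the first can serve as the denominator of a rate that includes women who decline. In the Data analysis section, eligible should therefore mean the criteria that can be checked at approach.

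**The case against.** The best defence is that there is only one definition. The Primary objective section states it explicitly, and the Data analysis sentence can be read as saying which log data will be used. Since the research fellow approaches women already called eligible, the two groups might be meant as the same. This stands in part. A reader might infer that the analyst is free to choose a denominator after seeing the counts; the article does not support that, because it gives an explicit definition. The defence does not remove the conflict: approach is limited to women who agreed to be seen, the log separates eligible from invited women, and the criterion is worded on the other group.

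Other stronger readings are tempting and are not supported:

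- **That the numerator is equally open, between consented and randomised.** The defined rate counts agreement to participate. The word recruited elsewhere is loose, but rates with randomised women on top are not the protocol's rate.
- **That the primary rate ought to be randomised women over all those identified.** That is a preference, and it would count women found ineligible in the run-in as recruitment failures.
- **That consent is known to precede the run-in.** This is only implied by the order of the Participant enrolment and Screening sections, and the flow chart is not shown. That full eligibility waits for the run-in is explicit.
- **That the verdict will flip.** With 70 approached and 90% of the pool approached it does not.

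It can also be said that this is a pilot, that the criterion has no formal stop or go rule attached, and that the rate is reported with a confidence interval. All true. But the interval expresses sampling error around one ratio. For 40/75 it is 0.533 ± 1.96 × √(0.533 × 0.467/75), that is 42.0% to 64.6%, and it does not tell the reader which ratio was meant to exceed 50%.

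**Conclusion.** The point holds as an inconsistency between the definition of a co-primary outcome and the criterion by which it is judged. It rests on the article's wording and needs no assumed figure.

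Its size does depend on assumptions. With 40 recruited, the verdict changes when the share of the eligible pool that is approached is at or below 93.75% (75 approached) or 87.5% (70 approached). If nearly all eligible women are approached, or the rate is well away from 50%, the choice of denominator does not matter. Because the protocol itself anticipates 50%, a modest gap is enough, and the matter should be settled before the counts are examined.

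The Sample size section shares the fault: its interval treats 40 as the denominator although 40 is the recruitment target.

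**What to change.** 1. **One primary rate.** Keep the rate in the Primary objective section and make it exact: women who agreed to participate, divided by women approached who meet the criteria checkable at approach (age, pain duration and site, laparoscopic diagnosis, no exclusion criterion). The run-in pain score plays no part in this denominator.
2. **One criterion.** Use the same wording in the Data analysis section in place of the eligible pool, and attach the >50% criterion to this rate only.
3. **Sample size.** Use the same rate there. If 40 is the number who agree, the denominator at 50% is 80 and the interval is about 39–61%. If 40 is meant as the number approached, say so; about 20 would then agree.
4. **Other steps reported separately, each with a 95% confidence interval:** approached over eligible pool, and randomised over consented (run-in pass). This shows the losses before approach and during the run-in, and keeps the primary rate from being read as overall uptake.

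Cost: wording changes in three sections, and one or two added fields in the participant log, which does not list consented and randomised women separately. The separate step rates will give a less favourable picture of overall uptake than the primary rate alone.

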### Secondary objectives

Estimation of variability of responses for sample size calculationAcceptability of proposed methods of recruitment, randomisation, treatments and questionnaires

### Inclusion criteria

Women are eligible for inclusion if they are as follows:Aged between 18 and 50 years.Pelvic pain of > 3 monthsPain located within the true pelvisEndometriosis diagnosed macroscopically by laparoscopyA numerical rating average ‘worst’ pain score (NRS) of greater than or equal (≥) to four (see below for details).

### Exclusion criteria

Women are excluded if they have one or more of the following:Unable to take/allergic to fish/PUFA/peanuts/soyabeanInsulin-dependent diabetesPregnancyTaking anticoagulantsBreast feedingUnable to give informed consent

### Co-primary outcomes

Recruitment and retention rates

### Secondary outcomes

Estimation of variability of responses to inform the primary outcome of the future definitive RCTAcceptability of proposed methods of recruitment, randomisation, treatments, and questionnaires

### Participant enrolment

All gynaecology consultants within NHS Lothian will be sent an email informing them of the study and requesting permission to approach their patients. A clinical research fellow will approach eligible women who have agreed to be seen by the trial team, while the women are still in the clinic, provide them with patient information sheets and offer them the opportunity to discuss the trial. Consent will only be taken later once the patient has had ample time, of at least 24 h, to read the patient information sheet. A further appointment will be arranged for the participant to come for this visit.

### Screening

Eligibility for randomisation will be based on the worst of four weekly numerical rating scale (0–10; NRS) pain scores collected by text messaging (‘run-in phase’), score of 4 out of 10 in 2 or more weeks is required. Texts will be sent by the clinical research fellow to the women’s mobile phone, asking about average and worst pain, respectively, and the woman will be asked to reply to the text message with her pain score, rating it from 0 for no pain at all, to 10 being worst pain imaginable. To capture known cyclicity in pain in women, these texts will be sent once per week during the eligibility phase (weeks–minus one to minus four). If a woman has an NRS of greater than or equal to ≥ 4 in two or more of the pre-randomisation run-in weeks of the study, she will be eligible for randomisation.

### Intervention

Women will be randomised to one capsule of Omacor 1000 mgs capsules (Omega-3-acid ethyl ester filled capsules) or one capsule of comparator (olive oil soft gelatin capsules which do not contain Omega-3 PUFA) to be taken twice a day, once in the morning and once at night with food. The allocated treatments will be taken for 8 weeks. Omega-3 purified fatty acids have been used clinically, e.g. post myocardial infarction and for hypertriglyceridemia at doses of 1000–4000 mg daily (in divided doses of 1000 or 2000 mg) [10]. However, high dosage (i.e. 4000 mg) has been associated with a moderate increase in bleeding time [11], so we chose to pilot a lower dose and frequency of one capsule (1000 mg) twice a day. We approached the MHRA for advice, and due to the fact that both PUFA and olive oil are ‘food supplements’, our trial was not deemed a CTIMP.

### Randomisation

The randomisation scheme will be generated using tables, drawn up by an independent statistician, with 1:1 allocation ratio. The allocated treatment codes will be put into sealed consecutively numbered opaque envelopes. When a woman is randomised into the study, she will receive the treatment indicated in the next available envelope.

### Data collection tools

#### Pain scores

During the treatment phase of the study, pain scores will be collected once a week by text messaging during last 4 weeks of the treatment phase (weeks 5 to 8) using the same study procedures as during the ‘run-in phase’.

#### Questionnaires

Women will be given the questionnaires below to complete at baseline and 8 weeks. Baseline demographic and clinical characteristics of the participants will also be recorded at baseline.Brief Pain Inventory (BPI) [12]12-Item Short-Form Health Survey (SF-12) [13]Pain Catastrophizing Questionnaire (PCQ) [14]Pain DETECT™ [15]Sexual Activity Questionnaire (SAQ) [16]Brief Fatigue Inventory (BFI) [17]General Health Questionnaire-12 (GHQ-12) [18]Work and Productivity Impairment Questionnaire-specific Health Problem Version 2.0 (WPAI-SHP) [19]

An additional acceptability questionnaire will be completed at the end of the study only. This questionnaire will also include questions about whether participants believed that they were receiving Omega-3 PUFA or olive oil, the acceptability of the allocated medication/treatment regimens (and compliance) and on the acceptability of completing trial-specific procedures including the questionnaires. All questionnaires will be anonymised and self-completed in private.

